#### Initial interview.

The interview will start with a questionnaire adapted from Lichen et al. (2021) and McCusker et al. (2018) [2,3].

**Table pone.0332773.t001:** 

Questions adapted from Lichen et al. (2021)			
* Question *		* Response options *	
*During your stay in the ED, what was your average comfort level?*		Very comfortable; Comfortable; Somewhat comfortable; Somewhat uncomfortable; Uncomfortable; Very uncomfortable	
*As a person in the emergency department, do you feel you were offered care specific to your individual needs (I.e. needs related to communication, hearing, vision, etc.)?*		Strongly agree; Somewhat agree; Neither agree nor disagree; Somewhat disagree; Strongly disagree	
Additional questions in the post-implementation phase			
*Did you use any of the items or services offered in the Geriatric Cart?*		Yes; No	
*Knowing that these items or services were available, even if I did not use them, made me feel more comfortable*		Strongly agree; Somewhat agree; Neither agree nor disagree; Somewhat disagree; Strongly disagree	
*The items I requested from the comfort cart made me feel more comfortable during my visit today*		Strongly agree; Somewhat agree; Neither agree nor disagree; Somewhat disagree; Strongly disagree	
*Having the comfort cart available improved my overall experience today*		Strongly agree; Somewhat agree; Neither agree nor disagree; Somewhat disagree; Strongly disagree	
*Having the comfort cart gave me more independence during my visit today*		Strongly agree; Somewhat agree; Neither agree nor disagree; Somewhat disagree; Strongly disagree	

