**Table pone.0332773.t003:** 

Questions adapted from Lichen et al. (2021)	
* Question *	* Response options *
*During the patient’s stay in the ED, what was his/her average level of comfort?*	Very comfortable; Comfortable; Somewhat comfortable; Somewhat uncomfortable; Uncomfortable; Very uncomfortable
*I feel that age-friendly care specific to the geriatric patient’s needs was provided*	Strongly agree; Somewhat agree; Neither agree nor disagree; Somewhat disagree; Strongly disagree
*I currently have access to non-pharmacological resources to provide comfort for geriatric patients*	Strongly agree; Somewhat agree; Neither agree nor disagree; Somewhat disagree; Strongly disagree
*Offering non-pharmacological resources to my patient increases my work burden by too much*	Strongly agree; Somewhat agree; Neither agree nor disagree; Somewhat disagree; Strongly disagree
Additional questions in the post-implementation phase	
*The Geriatric Cart and Menu of Items are a non-pharmacologic way to provide comfort*	Strongly agree; Somewhat agree; Neither agree nor disagree; Somewhat disagree; Strongly disagree
*The Geriatric Cart and Menu of Items are an important part of a comprehensive approach for improving patient satisfaction*	Strongly agree; Somewhat agree; Neither agree nor disagree; Somewhat disagree; Strongly disagree
*The Geriatric Cart and Menu of Items help increase my ability to care for older adults in a more compassionate way*	Strongly agree; Somewhat agree; Neither agree nor disagree; Somewhat disagree; Strongly disagree
*Having a hearing amplifier, reading glasses or magnifying glasses available for use helps patients feel more oriented/ less confused*	Strongly agree; Somewhat agree; Neither agree nor disagree; Somewhat disagree; Strongly disagree

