### Intervention

The comfort menu and cart will be implemented after the pre-intervention data collection phase is completed. The menu will list the items available on the cart and will be presented to eligible patients in printed or digital format (on a tablet). The cart will be placed in an easily accessible area within the ED. Approximated retail prices have been previously reported [3].

A one-month dedicated rollout period will precede the commencement of post-intervention participant enrollment. This phase is designed for comprehensive staff training on the proper use and components of the comfort menu and cart, including familiarization with all available items and menu options. Additionally, this period will ensure all necessary equipment is adequately prepared and any potential logistical challenges associated with the cart’s implementation are identified and resolved, thereby optimizing the fidelity and effectiveness of the intervention before data collection for the post-intervention group begins.

Comfort Cart Contents:

Hot and cold packs;Extra blanket and pillow;Face towel;Gloves and hat;Personal hygiene kit (toothbrush, toothpaste, cotton swabs, sleep mask, comb, deodorant, hand lotion);Items for distraction (magazines, word search puzzles, playing cards, coloring pages);Items to enhance communication (reading glasses, magnifying glass, penlight, cell phone charger, notepad, sound amplification device).

Comfort Menu Options:

Physiotherapy assessment;Conversation with chaplain, concierge, or social worker;List of resources for older adults needing community services;Home care assistance.

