### Data management and statistical analysis

All study data will be collected and managed using Research Electronic Data Capture (REDCap) [30], a secure web-based application. Research assistants will use tablets with online access to the REDCap database for direct data entry and informed consent procedures.

For the primary objective evaluating the impact of the comfort menu and cart on the experience of older patients we will use the questionnaire adapted from Lichen et al. (2021) and McCusker et al. (2018). For the secondary objectives evaluating the impact of a comfort menu and cart on the experience of medical and multidisciplinary staff involved in caring for older patients treated in the ED, we will use the the questionnaire adapted from Lichen et al. (2021).

Data analysis will be performed using Stata version 17 (StataCorp, College Station, TX). All statistical tests will be two-tailed with an alpha error of 0.05. Numerical variables will be reported as means and standard deviations or medians and interquartile ranges (IQR) depending on their distribution, which will be assessed visually and using the D’Agostino-Pearson test for normality. Categorical variables will be described as absolute counts and proportions. Numerical variables will be compared using Student’s t-test or ANOVA for normal distributions and Wilcoxon or Kruskal-Wallis tests for non-normal distributions. As appropriate, categorical variables will be compared using the chi-square test or Fisher’s exact test. Analyses will be adjusted to account for potential confounding variables, such as baseline frailty, cognitive impairment, and clinical severity. Missing data will be handled though mixed effects model.

All relevant data from this study will be made available upon study completion.

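### The single use question pools cart items with menu services, so service-only users cannot be separated from the patients who rate the items they requested (minor; descriptive post-phase data only)

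*Protocol article*

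**What the plan says.** All references are to the Methods of the protocol article.

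- **Use.** Under Initial interview, the additional post-implementation questions contain one question on use, answered Yes or No: "Did you use any of the items or services offered in the Geriatric Cart".
- **Rating of requested items.** The same block asks for agreement with "The items I requested from the comfort cart made me feel more comfortable during my visit today". The printed answers are five levels of agreement, with none for a patient who requested nothing.
- **Neighbouring statement.** The statement just before it does allow for non-users: "Knowing that these items or services were available, even if I did not use them, made me feel more comfortable".
- **What is offered.** Under Intervention, the cart contents are seven groups of physical goods. The menu options are a separate list: "Physiotherapy assessment;Conversation with chaplain, concierge, or social worker;List of resources for older adults needing community services;Home care assistance".
- **Role of the questionnaire.** Data management and statistical analysis states: "For the primary objective evaluating the impact of the comfort menu and cart on the experience of older patients we will use the questionnaire". The questions at issue belong to that questionnaire but have no pre-phase counterpart.

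**The concern.** The use question covers two kinds of help with one answer. A Yes may mean a blanket, a conversation with a social worker, or both. The later rating concerns only one kind, the items requested from the cart. The use question is the obvious filter for that rating, but it does not identify the patients to whom the rating applies.

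Two descriptive results are at stake. One is uptake, which another emergency department would want to know separately for goods and for services before adopting the bundle. The other is the proportion of item requesters who found the items comforting. Neither can be read cleanly from the questions as printed. The article names no other source that would supply the split: the staff questions do not record use by component, and the chart and administrative review extracts only length of stay and costs.

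**Working it through.** The plan gives no figure on this point, so there is none to reproduce. The check compares the wording and then illustrates the size.

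**Who can answer what, as printed**

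| Patient | Use question | Item to rate? | Kept after restricting to Yes? |
|---|---|---|---|
| Used an item, with or without a service | Yes | Yes | Yes, correctly |
| Used nothing | No | No | No, correctly |
| Used a service only | Yes (a service was used) or No (nothing came from the cart) | No | Kept if Yes, wrongly |

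Only the third row causes trouble. A skip rule keyed to the printed Yes/No and a filter applied in analysis give the same result, and neither removes service-only patients who answered Yes.

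**Inputs**

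- Post-phase group: 132 (Sample size calculation).
- Assumed: about 40% use an item, 0.40 × 132 = 52.8, taken as I = 53.
- Assumed: about 90% of these agree with the rating, 0.90 × 53 = 47.7, taken as A = 48.
- Assumed: S = 7, 13 or 20 service-only users (5.3%, 9.8% or 15.2% of 132), all answering Yes.

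**Agreement among patients answering Yes.** The target is A / I = 48/53 = 90.6%.

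If service-only users choose the neutral option (or disagree), the reported figure is A / (I + S):

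- S = 7: 48/60 = 80.0%
- S = 13: 48/66 = 72.7%
- S = 20: 48/73 = 65.8%

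If they all agree instead, it is (A + S) / (I + S): 55/60 = 91.7%, 61/66 = 92.4% or 68/73 = 93.2%. If they all answer No to the use question, the filter works and the figure is 48/53 = 90.6%. The size of the error therefore depends on how these patients answer, and the data would not show which case applies.

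**Uptake.** With 53 item users, the count of Yes answers lies between 53 (40.2% of 132) and 53 + S = 60, 66 or 73 (45.5%, 50.0% or 55.3%), depending on how service-only users read the question. Service uptake cannot be recovered from any of these counts, because an item user who also used a service gives the same Yes.

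**The case against.** The strongest reply is that this is form-level detail. A trained assistant conducts the interview and enters answers directly into REDCap, so branching or a not-applicable code may exist without being printed in an article. Even without one, the analyst can drop patients who answered No. This largely stands. A reader might infer that every patient who requested nothing contaminates the rating, for example 48/132 = 36% agreement with 53 requesters. That figure requires the analyst to ignore the use answer recorded in the same interview, and nothing in the article suggests this. What remains is the service-only group, which the printed filter cannot remove.

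A second reply is that the cart's name can stand for the whole package, and that the question mentions services expressly, so a service-only user would naturally say Yes. That is a fair reading. It makes the question a reasonable measure of any use, but it also puts every service-only user into the rating group.

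Third, the objectives treat menu and cart as one intervention, so pooling use is legitimate for the main question. That stands too. The rating, however, is specific to cart items and needs an item-specific filter.

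The exclusion of patients who decline to use the menu and cart may reduce the number of non-users. It does not remove service-only users, who have used the menu.

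A reader might also see a contradiction in the Intervention section, where "The menu will list the items available on the cart and will be presented to eligible patients in printed or digital format" does not mention services. The same section heads the services as menu options and covers staff training "including familiarization with all available items and menu options". That sentence and the staff questionnaire's label for the menu are editorial matters and form no part of this point.

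**Conclusion.** The point holds as a minor one, limited to descriptive post-phase data. As printed, item uptake cannot be told from service uptake, and service-only users who answer Yes are asked to rate items they never requested. With 53 item users and 7 to 20 service-only users answering Yes and then neutral, agreement would read 80% to 66% against 91%. Every rate in that illustration is assumed; only the group size of 132 comes from the protocol. The error is zero if there are no service-only users, if they all answer No, or if the form already contains an item-specific skip rule or answer option.

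Because the questionnaire serves the primary objective, a reader might infer that the primary result is at risk. The documents do not support that: these questions are asked only after implementation and cannot enter the before-after comparison.

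**What to change.** Before recruitment starts in April 2026:

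1. Replace the single use question with two Yes/No questions, one on any cart item and one on any menu service.
2. Add an answer for patients who did not request any item to the requested-items rating, or ask it only of patients who used a cart item, and state which rule applies.
3. Report both uptakes descriptively. Use is self-selected, so they should not be read as the effect of items or of services.

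The cost is one more question, one response option or skip rule in REDCap, and slightly less comparability with the questionnaire from which the items were adapted. No extra patients are needed.

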**Questions adapted from McCusker et al. (2018)**			
* Question *	* Response options indicating no problem *		* Response options indicating problem *
*Do you feel that the ED staff did everything they could to relieve your pain or discomfort?*	Yes, definitely; No pain (not applicable)		No; Somewhat; Don’t know
*Did the staff treat you with respect and dignity while you were in the ED?*	Yes, definitely		No; Somewhat; Don’t know
*Was your health problem explained to you in a way that you could understand?*	Yes, definitely; It is still being investigated; It was not necessary		No; Somewhat; Don’t know
*Did someone explain to you the tests you had to have?*	Yes, every time; It was not necessary		No; Sometimes; Don’t know
*If your family member wanted to talk to a doctor, did they have the opportunity to do so?*	Yes; I do not have a family member present; It was not necessary		No; Don’t know
*Before you left, did a staff member provide your family member or friend, who was with you in the ED, all the information they needed to help you recover?*	Yes, definitely; It is still being investigated; I do not have a family member present; It was not necessary		No; Don’t know
*Were you told what signs related to your health problem to watch out for when you get home?*	Yes, definitely; It is still being investigated; My family member was informed; It was not necessary		No; Somewhat; Don’t know
*Were you given advise about resuming your normal daily activities?*	Yes, definitely; It is still being investigated; My family member was informed; It was not necessary		No; Somewhat; Don’t know

The following data will then be collected:

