### Patient and public involvement

While patients or the public were not directly involved in the drafting of this specific study protocol, the study’s core components are founded on patient-centered principles. The comfort cart intervention is adapted from the work of Lichen et al. (2021), which was developed to address needs identified by older adults and included the patient’s voice in the selection of the items for the comfort cart. Furthermore, the primary patient experience outcome measures are adapted from the questionnaire developed by McCusker et al. (2018), which was created through direct qualitative interviews with older adults about their emergency department experiences. We will disseminate the study findings to patient communities and participants upon completion of the research.

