### Ethics and dissemination

Ethical approval for this study has been granted by the Institutional Review Board of HSL (*Comitê de Ética em Pesquisa do Hospital Sírio Libanês/ Sociedade Beneficente de Senhoras*): certificate n^o^ 85870125.4.0000.5461, decision n^o^ 7.436.261, dated March 12 2025. All participants, or their legal representatives for those with cognitive impairment, will provide written informed consent before any study procedures are initiated.

Given that the study employs a quasi-experimental design, with no alteration to the participants’ clinical procedures, and includes participants both before and after the intervention, the informed consent form will not disclose details of the intervention in order to mitigate information bias. The purpose is to ensure that participants are unaware of the intervention studied, thereby preventing their perception of care from being affected by a perceived comfort, either absent or present, depending on their study phase.

The results will be shared with the academic community through peer-reviewed publications and presentations at relevant conferences to inform future clinical practice and research.

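### The cart questions are printed before the eight care-problem items in the post phase only, and seven of those items count not-yet or not-applicable answers as no problem

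*Protocol article*

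**What the plan says.** The Initial interview section states that the interview opens with a questionnaire adapted from two earlier studies: the original comfort-cart study and a study of older adults' problems with emergency department (ED) care. The table prints, in this order:

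1. two items asked in both phases (average comfort, and care specific to individual needs);
2. five further items under the label "Additional questions in the post-implementation phase";
3. eight care-problem items, with answers sorted into a no-problem and a problem column.

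One of the five added items asks neutrally whether anything from the cart was used. The other four are agree/disagree statements worded in the cart's favour, for example "Having the comfort cart available improved my overall experience today". Mood, quality of life, function and cognition are collected after the questionnaire.

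The section on data management and statistical analysis assigns the whole questionnaire to the primary objective. The section on patient and public involvement describes the primary experience measures as coming from the care-problem instrument.

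The item beginning "Before you left, did a staff member provide your family member or friend" lists as no-problem answers "Yes, definitely; It is still being investigated; I do not have a family member present; It was not necessary". The Recruitment section has the research assistant enrol patients in the ED; the article does not tie the interview to discharge or disposition.

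Under Ethics and dissemination, the consent form withholds details of the intervention: "The purpose is to ensure that participants are unaware of the intervention studied".

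**The concern.** There are two separate issues, both within the primary patient-experience measure.

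**Order.** In the printed sequence, only post-phase patients judge statements praising the cart just before they rate pain relief, respect and information. Favourable statements can colour the answers that follow, and here they could do so in one phase only. The reported mood, quality-of-life and cognition measures come later still. The order also works against the plan's own reason for withholding the intervention at consent, which is to keep perceived comfort from shaping the answers.

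**Scoring.** A patient still under work-up, with no relative present, without pain, or for whom the step was not needed had no occasion for the problem to arise. Counting that patient as free of the problem mixes opportunity with quality of care. Three items concern leaving the ED or resuming life at home, yet the interview may take place before work-up ends; the still-under-investigation option itself implies this. The result is dilution of any real difference, and distortion if the mix of such patients changes between the two calendar phases.

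**Working it through.** **Item count (Initial interview table).**

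| Care-problem item | Not-yet or not-applicable answer in the no-problem column |
|---|---|
| Pain relief | no pain |
| Respect and dignity | none |
| Health problem explained | under investigation; not needed |
| Tests explained | not needed |
| Family access to a doctor | no relative present; not needed |
| Family given information | under investigation; no relative present; not needed |
| Warning signs | under investigation; not needed |
| Resuming activities | under investigation; not needed |

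Seven of eight items are affected, and under-investigation appears in four. The answer that a relative was informed, offered for the last two items, is a genuine no-problem answer and is not at issue.

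**Inputs.** 132 patients per phase (Sample size calculation) and a two-sided 5% level (statistical analysis section). The article gives no problem rates and no not-applicable shares, so every rate below is an assumption. There is no stated power figure for these items to reproduce: the 132 rests on a difference on a 1-to-6 scale.

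**Formulas.** If a share q is not applicable and coded as no problem, recorded rate = true rate × (1 − q). The chance of a significant result in the stated direction is Φ(|p1 − p2| / SE − 1.96), with SE = √{[p1(1 − p1) + p2(1 − p2)] / n}.

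**Dilution, same share in both phases.** Take true rates of 40% and 25% and q = 50%.

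- As coded: 0.40 × 0.5 = 0.20 and 0.25 × 0.5 = 0.125, with n = 132. SE = √[(0.16 + 0.1094)/132] = 0.0452; 0.075/0.0452 = 1.66; Φ(−0.30) = 38%.
- Excluded: 0.40 and 0.25, with n = 66. SE = √[(0.24 + 0.1875)/66] = 0.0805; 0.15/0.0805 = 1.86; Φ(−0.10) = 46%.

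The recorded difference halves, from 15 to 7.5 points. Using the pooled null error SE0 = √[2p̄(1 − p̄)/n] in Φ((d − 1.96·SE0)/SE) gives Φ((0.075 − 0.0890)/0.0452) = 38% and Φ((0.15 − 0.1598)/0.0805) = 45%, so the choice of formula hardly matters.

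**False difference, true rate 40% in both phases.**

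| q pre / post | Recorded rates | Chance of a significant apparent improvement |
|---|---|---|
| equal | equal | 2.5% (nominal) |
| 20% / 35% | 32% vs 26% | 0.06/0.0557 = 1.08; Φ(−0.88) = 19% |
| 20% / 45% | 32% vs 22% | 0.10/0.0543 = 1.84; Φ(−0.12) = 45% |

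**Order effect.** The article gives nothing from which to estimate it. For scale only: if the block lowered a reported problem rate from 40% to 35% with no true change, SE = √[(0.24 + 0.2275)/132] = 0.0595, 0.05/0.0595 = 0.84 and Φ(−1.12) = 13%.

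**The case against.** The strongest reply is that a journal table groups items by source and is not the REDCap form. The order of administration is therefore inferred from layout. That is right, and it makes the order point conditional. Still, no other order is given, and nothing in the article contradicts the printed one.

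A reader might infer several stronger things that the article does not support:

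- **That the eight items cannot be compared between phases.** Their wording, answers and scoring are identical in both. What exists is a risk of an order effect, with neither its presence nor its size shown.
- **That the whole primary measure is affected by the order.** The two common comfort items precede the cart block. They include the six-category comfort question, which matches the scale used for the sample size.
- **That the block unmasks patients.** Under Intervention, the menu is presented to eligible patients, so they already know of the cart. The consent rule concerns what the form discloses. The block adds salience just before the ratings, which is a weaker conflict with the rule's purpose.
- **That the scoring by itself manufactures an improvement.** It does so only if the not-applicable share falls differently in the two phases. The setting and recruitment pattern are the same in both, and the 35% and 45% shares above have no basis in the article. Against this, the phases are consecutive, unrandomised quarters, and the confounders named as examples (frailty, cognitive impairment, severity) do not include interview timing or companion presence.

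Counting a step that was not needed as no problem is also a defensible coding. Leaving such answers out conditions on something observed after exposure. Both remarks stand, and they are why the printed coding should be kept alongside. Finally, the family-information item lacks an intermediate answer, but it does so in both phases, so the comparison is untouched.

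**Conclusion.** The point holds as a risk worth removing. If the form follows the printed order, eight items of the primary patient-experience measure, and the mood, quality-of-life and cognition measures after them, are exposed to priming in the post phase only. The size is unknown.

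The scoring of seven items dilutes a true difference whenever some patients are not applicable. In the example above, leaving those answers out restores the 15-point contrast but recovers only about 8 points of power, so the main gain is an interpretable estimate. This assumes that being not applicable is unrelated to the problem rate among the rest. Bias between phases from the scoring is conditional on unequal shares; reporting the shares would settle whether it occurred.

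**What to change.** In the REDCap form:

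1. Ask the five cart questions after every item and scale common to both phases, and state that order in the protocol.
2. Record under-investigation, no-relative-present, not-needed and no-pain answers as a separate category, and report its share for each item by phase.
3. Analyse each item with that category outside the denominator, and keep the printed coding as a sensitivity analysis.

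The timetable runs REDCap development up to March 2026, with recruitment from April 2026, so the change is nearly free if made before then. The costs are denominators that differ by item and scores that no longer match the printed coding.

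Moving the three leaving-the-ED items to the 30-day call is not part of this recommendation: it would fit their wording better but would add recall error and losses to follow-up.
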